### 4.1. Sample Analysis

Sample size was calculated according to the improvement rate of MOS grade after 12-week training using PASS 2019 software. According to the preliminary experiment, the improvement rate of MOS in the CG was 20% and that of women in EG was 60% at 6 months postpartum. Group sample sizes of 106 in each group achieve 90.248% power to detect a difference between the group proportions of 0.4. The CG proportion is 0.2. The EG proportion is assumed to be 0.4 under the null hypothesis and 0.6 under the alternative hypothesis. The test statistic used is the one-sided Z test (unpooled). However, in considering 20% of the possible dropout, a total of 260 women will be randomized.

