### 4.2. Statistical Analysis

Data will be analyzed using SPSS version 26.0 (SPSS, Inc., Chicago, IL, USA) and the statistically significant difference will be identified if *p* < 0.05. Descriptive statistics including numbers and proportions, means and standard deviations, or medians (P25, P75) will be used. Group differences in the primary and secondary outcomes will mainly use chi-square and student’s t tests. For primary outcome, we will count the rate of pelvic muscle strength reaching grade 4 at 6 months postpartum between EG and CG by chi-square test or Fisher’s exact test as appropriate. Analysis of the primary and secondary outcomes will be based on an intention-to-treat basis in consideration of the drop-offs from the follow-ups and be conducted by the statistician at Peking University Clinical Research Institute. For comparison between groups of quantitative data, the analysis of variance or Wilcoxon rank sum test will be used according to the data distribution; chi square test or exact probability method is used for counting data (if chi square test is not applicable), Wilcoxon rank sum test or CMH test is used for grade data, and logistic regression analysis is used for correlation analysis. Repeated ANOVA will be used to assess within-patient correlation. and multivariable linear regression models if potential confounders were imbalanced.

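### The sample size is computed against a 20-point null difference, but the planned primary test is of zero difference, so the stated null and power belong to a different test

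*Protocol article*

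**What the plan says.** Section 4.1 (Sample Analysis) takes its rates from a preliminary experiment: "the improvement rate of MOS in the CG was 20% and that of women in EG was 60% at 6 months postpartum". It then fixes the hypotheses. For the control group, "The CG proportion is 0.2". For the experimental group, "The EG proportion is assumed to be 0.4 under the null hypothesis and 0.6 under the alternative hypothesis". The result is given as "Group sample sizes of 106 in each group achieve 90.248% power to detect a difference between the group proportions of 0.4", and the method as "The test statistic used is the one-sided Z test (unpooled". No alpha is stated for this calculation. With a 20% dropout allowance the total is set at 260.

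Section 4.2 (Statistical Analysis) says: "Group differences in the primary and secondary outcomes will mainly use chi-square" and t tests. The main comparison is described thus: "we will count the rate of pelvic muscle strength reaching grade 4 at 6 months postpartum between EG and CG by chi-square test". Fisher's test is the stated alternative. The criterion is that "the statistically significant difference will be identified if *p* < 0.05". No margin appears there. The hypotheses in the Introduction and the Abstract say only that the workout would improve pelvic floor muscle strength, or is effective in strengthening it.

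**The concern.** With CG at 0.2 and EG at 0.4 under the null, Section 4.1 tests whether the benefit exceeds 20 percentage points. A chi-square or Fisher test comparing two rates asks whether there is any difference at all. These are different hypotheses with different rejection regions, both attached to one primary outcome.

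Two things are at stake. First, the power that justifies the sample size is not the power of the test that will be run. Second, the criterion for success is ambiguous. A result between the two thresholds meets Section 4.2 but leaves the null of Section 4.1 standing, and the article does not say which of the two governs the conclusion.

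**Working it through.** **Inputs.** From Section 4.1: CG 0.20; EG 0.40 under H0 and 0.60 under H1; 106 per group; one-sided Z test, unpooled; 20% dropout; 260 randomized, so 130 per arm, or 130 × 0.8 = 104 if only completers are analysed. From Section 4.2: chi-square or Fisher test, p < 0.05 (taken as two-sided; sidedness is not stated).

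**1. Reproducing the stated power.** Null difference = 0.40 − 0.20 = 0.20; true difference = 0.60 − 0.20 = 0.40.

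- SE = √[(0.2×0.8 + 0.6×0.4)/106] = √(0.40/106) = 0.06143
- Power = Φ[(0.40 − 0.20)/0.06143 − 1.960] = Φ(3.256 − 1.960) = Φ(1.296) = 0.90248

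This agrees with 90.248% to every digit. Other readings do not: one-sided 0.05 gives 94.6%, pooled variance at one-sided 0.025 gives 84.4%, and exact enumeration at one-sided 0.025 gives 88.8%. The 0.4 null is therefore not a misprint. It is the value that produced 106 per group.

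**2. Power of the planned test at the same rates.** For equality, two-sided 0.05:

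Power = Φ{[Δ − 1.960·√(2p̄(1−p̄)/n)] / √[(p₁(1−p₁) + p₂(1−p₂))/n]}

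At 0.20 vs 0.60, Δ = 0.40 and p̄ = 0.40:

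| n per arm | Power |
|---|---|
| 106 | 99.999% |
| 30 | 90.6% |
| 29 | 89.6% |

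About 30 per arm (35 with continuity correction) would therefore give 90%.

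**3. How far apart the two criteria lie.** Take CG 21/106 = 0.198, close to the assumed 20%.

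| EG responders | Difference | Chi-square z (uncorrected) | Lower 95% limit (unpooled) |
|---|---|---|---|
| 33/106 | 0.113 | 1.89 | −0.003 |
| 34/106 | 0.123 | 2.04 | 0.006 |
| 55/106 | 0.321 | 4.87 | 0.199 |
| 56/106 | 0.330 | 5.00 | 0.209 |

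For 34/106: pooled p = 55/212 = 0.2594, SE = √(2×0.2594×0.7406/106) = 0.0602, z = 0.1226/0.0602 = 2.04. For 56/106: SE = √[(0.198×0.802 + 0.528×0.472)/106] = 0.0620, lower limit = 0.330 − 1.960×0.0620 = 0.209.

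Every EG count from 34 to 55 is significant under Section 4.2 but does not reject the null of Section 4.1.

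**4. What the planned numbers support under each single hypothesis**, if the quoted rates apply to the endpoint tested:

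| Test | 104 per arm | 130 per arm |
|---|---|---|
| Equality, 20% vs 40% | about 89% | about 95% |
| Equality, 20% vs 60% | > 99.9% | > 99.9% |
| Margin 0.20, 20% vs 60%, one-sided 0.025 | 89.7% | 95.0% |

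Margin row: Φ[0.20/√(0.40/104) − 1.960] = Φ(1.265) = 0.897; Φ[0.20/√(0.40/130) − 1.960] = Φ(1.646) = 0.950.

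**The case against.** The strongest defence is that the planned analysis fits the hypotheses that the article actually states. These concern improvement, not improvement by more than 20 points. The chi-square keeps its nominal error rate for that question, and the trial has more power for it than claimed. No planned analysis becomes invalid. All of this stands, and it limits the seriousness of the point.

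Four stronger readings are tempting, and the document does not support them.

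- **That the power was miscalculated.** The arithmetic is right for its own test. The fault is that this test is not the one planned.
- **That the phrase about detecting a difference of 0.4 is false.** Power was indeed evaluated at a true difference of 0.60 − 0.20 = 0.40. The phrase alone does not show that the null difference was 0.20, but the null is disclosed shortly afterwards.
- **That the chi-square has an inflated false-positive rate.** At 20% vs 40% it rejects equality about 89–90% of the time. At those rates the programme does raise the response, so rejecting equality is correct. The figure is power, not type I error.
- **That the trial is underpowered.** It is the reverse for the planned test.

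Nothing in the article announces a claim of benefit above 20 points, so misuse of a significant p-value in that way is a possibility and not a plan.

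**Conclusion.** The mismatch is real and should be fixed, though it does not invalidate the trial. Section 4.1 states a null and a power for a superiority test with a 0.20 margin, and Section 4.2 plans a test with no margin. At the design rates with 106 per arm, the stated power is 90.248% and that of the planned test is above 99.99%. The two success thresholds differ by 22 responders out of 106 (34 against 56, with CG at 21).

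The conclusion rests on these assumptions:

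- One-sided 0.025 for the sizing is inferred from the exact match.
- The p < 0.05 rule is read as two-sided.
- The 104-per-arm figures assume that only completers are analysed after 20% dropout. Section 4.2 specifies intention-to-treat, so up to 130 per arm may enter, and both are shown.
- The 20% and 60% are rates of MOS improvement, whereas the primary test counts women reaching grade 4. Since entry excludes only women above grade 3, a woman can improve without reaching grade 4. The powers in step 4 carry over only if the same rates hold for the endpoint tested.

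**What to change.** First settle one definition of the primary endpoint, MOS improvement or reaching grade 4, and confirm that the assumed rates refer to it. Then make Sections 4.1 and 4.2 test the same hypothesis, in one of two ways:

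1. **Equality (the simpler change).** Delete the 0.4 null from Section 4.1 and restate the calculation for the two-sided test of equality, with its alpha. This matches the stated hypotheses.
2. **Margin.** If a benefit above 20 points is to be claimed, name and justify the margin, and make the criterion in Section 4.2 a lower 95% confidence limit for the risk difference above 0.20.

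In either case report the risk difference with its 95% CI, and quote power for the number expected to be analysed.

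The cost is a rewording of both sections, one confidence interval, and the work of reconciling the endpoint. No additional patients are needed under either option. The drawback of the second is that its criterion is much harder to meet.

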### 4.2. Statistical Analysis

Data will be analyzed using SPSS version 26.0 (SPSS, Inc., Chicago, IL, USA) and the statistically significant difference will be identified if *p* < 0.05. Descriptive statistics including numbers and proportions, means and standard deviations, or medians (P25, P75) will be used. Group differences in the primary and secondary outcomes will mainly use chi-square and student’s t tests. For primary outcome, we will count the rate of pelvic muscle strength reaching grade 4 at 6 months postpartum between EG and CG by chi-square test or Fisher’s exact test as appropriate. Analysis of the primary and secondary outcomes will be based on an intention-to-treat basis in consideration of the drop-offs from the follow-ups and be conducted by the statistician at Peking University Clinical Research Institute. For comparison between groups of quantitative data, the analysis of variance or Wilcoxon rank sum test will be used according to the data distribution; chi square test or exact probability method is used for counting data (if chi square test is not applicable), Wilcoxon rank sum test or CMH test is used for grade data, and logistic regression analysis is used for correlation analysis. Repeated ANOVA will be used to assess within-patient correlation. and multivariable linear regression models if potential confounders were imbalanced.

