## 4. Outcomes of the Study

The primary outcome will be the comparison of participants’ pelvic floor muscle strengths using MOS scale at the enrollment baseline and post intervention. The secondary outcomes will be: (1) the occurrence of SUI, (2) the change of the Pelvic floor ultrasound indicators, (3) change of the Pelvic Organ Prolapse Quantitation measured by callipers, (4) change of the pelvic sagittal rotation degree, and (5) the change of the overall body composition and strength. The list of data collection instruments and time of data collection is presented in Table 2 and Table 3.

The other secondary outcome measures involved in the Table 2 will be calculated and discussed separately.

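### The sample size and 90.248% power rest on an undefined MOS improvement rate tested against a 0.20 margin, but the primary analysis is a chi-square test of the rate reaching grade 4

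*Protocol article*

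**What the plan says.** Three adjacent sections of the protocol article deal with the primary outcome.

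- **Section 4 (Outcomes of the Study)** describes it as a "comparison of participants’ pelvic floor muscle strengths using MOS scale at the enrollment baseline and post intervention". It names the scale and the time points but no summary measure.
- **Section 4.1 (Sample Analysis)** states: "Sample size was calculated according to the improvement rate of MOS grade after 12-week training". The preliminary experiment is the source of the rates: "the improvement rate of MOS in the CG was 20% and that of women in EG was 60% at 6 months postpartum". The hypotheses carry a margin: "The EG proportion is assumed to be 0.4 under the null hypothesis and 0.6 under the alternative hypothesis", with the control proportion at 0.2. The test is a one-sided unpooled Z test, with 106 per arm and 90.248% power. Alpha is not given. Allowing for 20% dropout, 260 women are randomized.
- **Section 4.2 (Statistical Analysis)** gives the primary analysis as follows: "we will count the rate of pelvic muscle strength reaching grade 4 at 6 months postpartum between EG and CG by chi-square test". Fisher's exact test is the alternative where needed. Significance is p < 0.05, with no sidedness and no margin.

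Two other places bear on this. Section 2.3 excludes only women above MOS grade 3, so grades 0 to 3 may enter (the abstract says below grade 3). Section 1 treats grades 4 and 5 as the normal condition.

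**The concern.** On its ordinary meaning, improvement in grade is not the same variable as reaching grade 4. A woman who goes from 1 to 2, or from 2 to 3, has improved but is not a success under Section 4.2. Under the abstract's entry rule, no one-grade gain could ever count as a success.

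The test differs as well. Section 4.1 asks whether the experimental rate exceeds the control rate by more than 0.20. Section 4.2 asks whether the two rates differ at all.

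Two things are at stake. A reader of the results could not tell whether a reported improvement rate or a reported grade-4 rate was the prespecified measure of success. And the only power figure in the document would not describe the analysis on which the conclusion will rest.

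**Working it through.** **1. Reproduce the stated power.** Inputs from Section 4.1: control 0.2, experimental 0.6, null difference 0.4 − 0.2 = 0.2, 106 per arm, unpooled one-sided Z.

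- SE = √[(0.2×0.8 + 0.6×0.4)/106] = √(0.40/106) = 0.0614
- Power = Φ[(0.6 − 0.2 − 0.2)/SE − z(1−α)]
- α = 0.025: Φ(3.256 − 1.960) = 0.90248, which matches the document
- α = 0.05: Φ(3.256 − 1.645) = 0.946, which does not match

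The arithmetic in Section 4.1 is sound, with an unstated one-sided alpha of 0.025. After 20% dropout, 260 × 0.8 = 208 women remain, or 104 per arm. The same formula then gives 89.7%.

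**2. Compare what is sized with what is analysed.**

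| | Section 4.1 | Section 4.2 |
|---|---|---|
| Response | Improvement in MOS grade, undefined | Reaching grade 4 |
| Null hypothesis | Difference of 0.20 | No difference |
| Test | Unpooled Z, one-sided | Chi-square or Fisher's exact |
| Alpha | Not stated (0.025 recovered) | 0.05, sidedness not stated |

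Both are binary rates at 6 months postpartum. They differ in the response definition as written, and in the null hypothesis whatever the definition.

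**3. Power of the planned test.** Assumption: chi-square at two-sided 0.05, with 104 per arm. The document gives no grade-4 rates. I therefore assume that a share f of the women who improve reach grade 4, the same in both arms, so the rates are 0.2f and 0.6f. With p̄ the mean of the two rates and n = 104:

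Power = Φ{[(pE − pC) − 1.960 √(2p̄(1−p̄)/n)] / √[(pC(1−pC) + pE(1−pE))/n]}

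For example, at 10%/30%: (0.20 − 1.960×0.0555)/0.0537 = 1.70, and Φ(1.70) = 0.955.

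| f | Control / experimental | Power |
|---|---|---|
| 1 | 20% / 60% | >99.9% |
| 0.75 | 15% / 45% | 99.8% |
| 0.5 | 10% / 30% | 95.5% |
| 0.33 | 6.7% / 20% | 81.2% |
| 0.25 | 5% / 15% | 67.4% |

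The fixed 1:3 ratio is itself an assumption. A narrower contrast gives less: 15%/30% has 74.7% with 106 per arm.

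**The case against.** The strongest reply is that improvement in Section 4.1 may simply mean reaching grade 4. Entrants are at most grade 3, Section 1 calls grades 4 and 5 normal, and both sections use a binary rate at the same time. The text allows this reading, so it cannot be asserted that the 20% and 60% belong to another endpoint, or that they are upper bounds for the grade-4 rates. What stands is that no sentence makes the link, and that the change of null hypothesis remains even on this reading.

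A reader might also infer several stronger points that the document does not support.

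- **Three rival primary endpoints.** Section 4 names the scale and time points only. The firm conflict is between Sections 4.1 and 4.2.
- **A free choice of test for MOS.** Section 4.2 does say "Wilcoxon rank sum test or CMH test is used for grade data", but this belongs to a general list of methods by data type. The specific sentence on the primary outcome takes precedence.
- **An underpowered trial.** Applying Section 4.1's margin test to assumed grade-4 rates with 104 per arm gives 42.7% at 10%/40%, 38.4% at 15%/45% and 14.6% at 10%/35%. Section 4.2 does not plan that test. The chi-square test has more than 99% power at all three pairs.

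Leaving detail to a separate analysis plan does not answer the point, because the article states both definitions itself and they do not agree.

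**Conclusion.** The point holds. The endpoint that sizes the trial is not shown to be the endpoint that will be analysed, and 90.248% is not the power of the planned primary test on any reading of improvement. If the pilot rates are grade-4 rates, the planned test has more than 99.9% power. If they are not, its power depends on rates that the document does not give: along the assumed 1:3 ratio it stays above 80% down to about 6.7%/20% and drops to about 67% at 5%/15%. These figures assume a two-sided 0.05 chi-square test and 104 per arm. The mismatch is therefore a defect in the definition and justification of the primary analysis, and not evidence that 260 women are too few. It deserves correction because it concerns the trial's main hypothesis, in an open-label design with an outcome graded by palpation.

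**What to change.** 1. Use one primary endpoint in Sections 4, 4.1 and 4.2: the proportion with MOS grade 4 or higher at the second assessment. Section 4.2 already designates grade 4, and Section 1 supports the threshold.
2. In Section 4.1, say whether the pilot's 20% and 60% are grade-4 rates. If not, re-tabulate the pilot for grade 4 or higher. If the pilot cannot supply these rates, give the power over a stated range of assumed rates.
3. Say whether the 0.20 margin applies to the analysis. If it does, Section 4.2 needs a test against that margin. If it does not, remove it from Section 4.1.
4. Restate the power for the test actually planned, with alpha and sidedness.
5. Report any improvement rate (with improvement defined) or ordinal MOS comparison as secondary.

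The cost is wording and a re-read of existing pilot data. The stated power figure will change. If the 0.20 margin is kept and the grade-4 rates prove lower than 20%/60%, the adequacy of the sample size would have to be looked at again.

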Pregnancy and vaginal delivery have independently been proved to be the risk factors for the development of severe urinary incontinent (SUI) as they could obviously weaken the pelvic floor muscle (PFM) strength. However, it was hard to evaluate patients’ muscle strength objectively; therefore, it was hard to validate whether a measure could be effective to have the weakened pelvic floor muscles be recovered before Modified Oxford scale (MOS) for muscle strength was published [3]. MOS provides quantitative scales for muscle strength, and it is simple and easy to apply clinically. It is becoming widely accepted method for pelvic floor muscle strength assessment since it was published. Literately and clinically, MOS 4 and 5 is identified as having “good” or “strong” muscle contraction which represents a normal condition of the pelvic floor muscles; relevantly MOS ≤3 indicates a weak contraction or no contraction being felt [4]. Some studies suggested that pelvic floor muscle strength be correlated with the incidence of pelvic organ prolapse (POP). Thus, Pelvic Organ Prolapse Quantification (POP-Q) was developed for evaluation of the pelvic floor muscle [5]. Borello-France et al. [6] used POP-Q to evaluated women’s pelvic floor muscle in their studies and argued that women with stage II of prolapse were better than those with stage III or IV in elevating their pelvic floor, and also would be easier to get benefit from PFM training than those over stage III. Scientific evidence showed that 10–20% of patients who were not intervened for the clinically confirmed POP got progressed in term of POP-Q scoring in 2-year follow-up [7,8], so early prevention or treatment should have high priority. The incidence rate of POP is higher in middle aged and elderly women. PFM training is recommended to women postpartum for it reduces the incidence of PFD during 6–12 months postpartum [9] and should possibly reducing the incidence of diseases from muscle dysfunction related to the anatomical changes with aging [10]. A program of supervised PFM training was recommended as a first option for women with symptomatic POP-Q stage I or stage II [11]. MOS and POP-Q can be the objective indicators be used to validate the effectiveness of any measure in improving PFM.

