### 2.3. Exclusion Criteria

Participants will be excluded if they are: (1) confirmed by postpartum pelvic examination to be >grade 3 of pelvic floor muscle strength by Modified Oxford Scale (MOS); (2) ≥stage III for Pelvic Organ Prolapse Quantification (POP-Q); (3) symptomatically confirmed to have severe urinary incontinence (Women with more than one incontinent episode per day AND an important volume of urine loss [28] or urine leakage occurred in a quiet state were classified as having severe urinary incontinence); or (4) any limb dysfunction that unenabled women to take this training. A participant will be recorded as“ drop off from trial” if she becomes pregnant during the follow-ups.

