**Cooling Down**	Dynamic stretching, including upper and lower limbs, waist, back, and abdomen stretching and pelvic floor muscle relaxation with mini foam axis.			

**Table 2 ijerph-19-11073-t002:** Data collection and follow-up instruments.

		EG	CG	EG	CG	EG	CG
Baseline screen, Informed consent, Randomization							
The follow-up visits		The First		The Second		The Third	
Demographic data collection		◯	◯				
The MOS		●	●	●	●	●	●
POP-Q stage		●	●	●	●	●	●
Cough stress test		●	●	●	●	●	●
Vaginal relaxity		●	●	●	●	●	●
Pelvic floor electrophysiological test		◎	◎	◎	◎	◎	◎
Pelvic floor ultrasound		◎	◎	◎	◎	◎	◎
Spine X-ray		◎	◎	◎	◎	◎	◎
Body Composition		◎	◎	◎	◎	◎	◎
Hand grip test		◎	◎	◎	◎	◎	◎
Trunk endurance test		◎	◎	◎	◎	◎	◎
Questionnaires	PFDI-20	◯	◯	◯	◯	◯	◯
	PFIQ-7	◯	◯	◯	◯	◯	◯
	FSFI-6	◯	◯	◯	◯	◯	◯
	IPAQ-SF	◯	◯	◯	◯	◯	◯
	PSQI	◯	◯	◯	◯	◯	◯
Training record				✷	✷(if any)		
RPE				✷			
Adverse Event				☐	☐		

●: Data would be collected by pelvic floor professionals via vaginal palpation. ◎: Data would be collected by experienced General specialists as the examiners. ◯: data would be collected by requesting all participants to give answers through scanning a QR code. ✷: Recording by all the participants in EG only per their training record and RPE score given by themselves.: Optional items. Abbreviations: MOS: The modified Oxford Scale [3], which needs to be performed by inserting two fingers into the vagina for approximately 4 cm to feel the FPM contraction and give scale ranging from 0 (no contraction) to 5 (strong contraction).; POP-Q [5]: pelvic organ prolapse quantitation; PFDI-20: The Pelvic Floor Distress Inventory Questionnaire-20; PFIQ-7: Pelvic Floor Impact Questionnaire-7; FSFI-6: The 6-item Female Sexual Function Index; IPAQ-SF; International Physical Activity Questionnaire Score-Short Form; RPE: Ratings of Perceived Exertion.

**Table 3 ijerph-19-11073-t003:** Outline of Soring for general pelvic floor function.

Testing Items	Indicators	Compute Value	Score Value
POP-Q	Stage 0	0	
	Stage I	1	
	Stage II	2	
	Stage III	3	
	Stage IV	4	
Cough stress test	Yes	1	
	No	0	
Vaginal relaxation	≥4 fingers	4	
	>3 fingers, and <4 fingers	3	
	=3 fingers	2	
	>2 fingers, and <3 fingers	1	
	≤2 fingers	0	
Pelvic floor electrophysiological test [40]	<20 cm^2^Hg	1	
	≥20 cm^2^Hg	0	
			* Total Score ^1^
PFDI-20	-	Comprehensive score	
PFIQ-7	-	Comprehensive score	
FSFI-6	-	Comprehensive score	
			* Total Score ^2^

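### The primary test on reaching MOS grade 4 is valid, but it ignores each woman's baseline MOS grade and so gives away precision that a prespecified stratified analysis would recover at no cost

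*Protocol article*

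**What the plan says.** Section 4.2 gives the primary endpoint its own sentence: "we will count the rate of pelvic muscle strength reaching grade 4 at 6 months postpartum between EG and CG by chi-square test", with Fisher's exact test as the alternative. This is a two-by-two comparison.

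Section 4 builds baseline into the outcome, since muscle strength is to be compared "using MOS scale at the enrollment baseline and post intervention". Table 2 schedules MOS for both arms at all three visits. The notes to Table 2 describe it as a palpation grade: "give scale ranging from 0 (no contraction) to 5 (strong contraction".

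Entry grades differ. Section 2.3 excludes women ">grade 3 of pelvic floor muscle strength by Modified Oxford Scale (MOS", which leaves grades 0 to 3. The abstract is narrower and admits only women below grade 3. On either wording, women start at different distances from grade 4.

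Section 2.5 describes a 1:1 randomisation list for each centre and states no stratification by MOS.

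Three other provisions in section 4.2 bear on the point:

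- A closing clause offers "multivariable linear regression models if potential confounders were imbalanced".
- A general rule says "Wilcoxon rank sum test or CMH test is used for grade data", with no stratum named.
- Logistic regression is listed, but for correlation analysis.

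**The concern.** Success is a fixed threshold. A woman who enters at grade 3 needs one step to reach grade 4; a woman who enters at grade 1 needs three. Baseline grade is therefore the obvious predictor of the primary endpoint, and it will be on file for everyone randomised. A crude comparison treats these women alike, so the variation in outcome that baseline explains stays in the error term.

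The one route to adjustment does not repair this. It is triggered by imbalance seen in the data, names no covariate, and is a linear model not tied to the binary primary endpoint. It also leaves open, after the data are seen, whether the primary result is adjusted and for what.

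At stake are the width of the confidence interval for the rate difference and the power for the 20-point margin on which section 4.1 sizes the trial.

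**Working it through.** **Inputs from section 4.1:** control rate 0.2; EG rate 0.4 under the null and 0.6 under the alternative; 106 per group; one-sided unpooled Z test; stated power 90.248%. No alpha is given there.

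**The plan's own figure.** Crude variance per woman per arm: 0.2×0.8 + 0.6×0.4 = 0.40. SE = √(0.40/106) = 0.0614. Power = Φ(0.2/0.0614 − 1.96) = 90.248% at one-sided alpha 0.025, so the figure reproduces. At one-sided 0.05 the result would be 94.64%. The crude 95% CI half-width is 1.96 × 6.14 = 12.0 points.

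**Assumptions, because the documents give no figures:** three entry grades (the lowest assumed grade, then two higher) with shares 20/40/40%, 10/30/60% or equal thirds, and an odds ratio of 1.5, 2, 3 or 5 per baseline grade for reaching grade 4. Within each scenario the marginal rates are held at 0.2 and 0.6. This treats the section 4.1 rates as rates of reaching grade 4.

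**Adjusted variance.** With w the share, c and e the control and EG success rates in a grade, and d = e − c:

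V_adj = Σ w[c(1−c) + e(1−e)] + Var(d)/2, and SE = √(V_adj/106).

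This is the variance of the risk difference standardised over baseline grade. With 1:1 allocation the Mantel-Haenszel weights are close to stratum size, so it is a fair guide to the stratified risk difference as well.

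**Worked case: equal thirds, odds ratio 3.** c = 0.062, 0.165, 0.373; e = 0.351, 0.619, 0.830. The within-grade term is 0.345 and Var(d)/2 is 0.003, so V_adj = 0.348. Ratio to crude: 0.348/0.40 = 0.870. SE = √(0.348/106) = 0.0573. Power = Φ(0.2/0.0573 − 1.96) = 93.7%.

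**All scenarios:**

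| Odds ratio per grade | Variance cut | Margin-test power |
|---|---|---|
| 1.5 | 1–2% | 90.6–90.8% |
| 2 | 4–6% | 91.3–91.9% |
| 3 | 8–13% | 92.5–93.7% |
| 5 | 15–23% | 94.1–95.9% |

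The weakest case has variance ratio 0.986, giving a half-width of 12.04 × √0.986 = 11.96 points. The strongest has ratio 0.773, giving 12.04 × √0.773 = 10.59. The equivalent number per group falls from 106 to between 105 (106 × 0.986) and 82 (106 × 0.773).

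**Validity of the crude test.** A simulation with no treatment effect, a common rate of 0.2, equal thirds and an odds ratio of 5 per grade gave type I error 0.050 and mean bias near zero.

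**Where chance imbalance sits.** The part of the crude difference due to chance imbalance in baseline MOS has SD √((0.40 − V_adj)/106), which is 0.7 to 2.9 points over these scenarios. That is exactly the variance that adjustment removes, and it already lies inside the crude SE of 6.14 points.

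**Power of the test that section 4.2 describes.** An ordinary two-sided chi-square with 106 per arm has power above 99.9% for 0.2 v 0.6, 89.4% for 0.2 v 0.4 and 68.9% for 0.2 v 0.35.

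**The case against.** The strongest reply is that an unadjusted chi-square is an acceptable primary test, and that covariate detail is commonly left to a full protocol or SAP that is not shown. The first half stands: nothing here makes the planned test invalid. The second does not dispose of the point, because section 4.2 states the primary test explicitly rather than deferring it.

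A reader might infer that an arm which happens to receive more grade-3 women would produce a result that the plan neither corrects nor allows for. The documents do not support that. The crude standard error allows for it, and counting the imbalance as a second harm would count the precision loss twice. Nor is the plan silent on imbalance, since it has the conditional regression clause; that clause is poorly fixed rather than absent.

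Two further objections limit the size. The gain in margin-test power belongs to section 4.1, whereas section 4.2 states no margin, and at 20% v 60% its ordinary chi-square leaves nothing material to recover. The link between baseline and outcome may also be weak: section 2.4 has different gynaecologists examining at different visits, so rater disagreement would dilute it, and at an odds ratio of 1.5 the gain is only 1–2%. Both stand as limits on the benefit. Neither is a reason to leave baseline out, since including it costs nothing.

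**Conclusion.** The point holds as one of efficiency and prespecification, not of bias or false positives. The primary test omits a predictor that is measured in every woman and tied to the endpoint by its definition, and the imbalance-triggered linear model does not make good the omission.

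The benefit is small to moderate: a 1% to 23% cut in variance, and at most about 1.5 points off a 12-point half-width (12.04 − 10.59 = 1.45). It rests wholly on the assumed baseline mixes and odds ratios. It matters if the margin hypothesis of section 4.1 is the one to be tested, or if the true effect is well below 40 points.

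Section 4.1 speaks of an improvement rate in MOS grade and section 4.2 of reaching grade 4. That mismatch is a separate issue, and baseline adjustment does not settle it.

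**What to change.** In section 4.2, name one primary analysis: a Mantel-Haenszel (CMH) comparison of the grade-4 rate stratified by baseline MOS grade, with sparse low grades pooled by a rule set in advance. Report the stratified risk difference with its 95% CI, which can also be read against the 20-point margin. Keep the crude chi-square or Fisher's exact test as a sensitivity analysis.

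State that observed imbalance will not trigger adjustment of the primary endpoint, and confine the linear-regression clause to continuous secondary outcomes.

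The cost is a sentence or two of text. No new data and no extra women are needed, and CMH is already among the methods listed in that section.
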